### Exploratory investigations

Where possible, we will collect blood samples at baseline and week 3 to measure the following:

Duloxetine serum trough concentration at week 3.^43 44^Pharmacogenomic testing (eg, CYP2D6) at baseline.^45^,^47^High-sensitivity c-reactive protein at baseline and 3 weeks.^48^

### Sample size

A sample size of 266 patients (133 per group) provides 90% power to detect a 1-point difference in leg pain intensity, measured on a 0–10 scale, between the duloxetine and placebo groups. The calculation assumes a SD of 2.5 based on previous duloxetine trials for back pain^15^ and uses a two-tailed alpha level of 5%. This sample size also provides more than 90% power to detect a clinically worthwhile difference of 3 points on the Roland-Morris Disability Sciatica Questionnaire, which is the trial’s key secondary outcome, assuming a conservative SD of 6.

To increase the chance of finding the correct answer early and minimise the expected sample size, we will use an adaptive group sequential design with O’Brien-Fleming efficacy and non-binding futility stopping boundaries.^49^ This approach is based on flexible ‘spending functions’ which adjust the level of alpha and beta spent based on the number of looks. It has the advantage that the exact number and timing of interim analyses does not need to be prespecified. Based on the 10 000 trial simulations with up to three optimally spaced looks (two interim analyses), this approach leads to an expected total sample size of 208 participants (an expected saving of 58 participants, or 22% of the sample size compared with a non-adaptive design) and, in the case of no early stopping, a maximum sample size of 282 participants (only 16 (6%) more participants than with a non-adaptive design) (figure 3). Allowing for a conservative estimate of 15% of dropouts based on tolerability data from our previous work, we will aim to recruit a maximum sample size of 332 participants.

**Figure 3 F3:**
[figure not shown]
Stopping boundaries (**a**) and probability of stopping at each interim analysis under the alternative hypothesis (**b**)

### Strategies for achieving adequate participant enrolment

We plan to recruit up to 100 study sites to screen and recruit participants. We will run advertising campaigns on social media platforms where respondents will be prescreened by the research team who will refer suitable respondents to the study sites. Other strategies to ensure the recruitment target is achieved will include regular phone, email and visit contact of the study sites by the research team to monitor progress and provide support, provision of study posters and brochures for the study sites to display, streamlined study procedures (screening, recruitment and follow-up) to reduce the workload of clinicians and participants, and reimbursement of study sites for the time spent on trial-related tasks.

### Data collection methods

A custom-built study database will be created in REDCap. Following an established process,^13 50^ we will use electronic data capture where data collected by phone will be directly entered into the database by research assistants, and data completed by participants online (via a secure website) will be automatically transcribed into the database.

### Data management

The integrity of data will be closely monitored for omissions and errors in the secure REDCap study database hosted by the University of Sydney.

### Statistical methods

Data analysis will be conducted blinded on an intention-to-treat basis that is, by analysing patients according to their randomised group regardless of post-randomisation events. It will be guided by a prespecified statistical analysis plan which will be made public prior to database lock. Analyses will be conducted and validated using randomly scrambled group allocations before unblinding.

#### Primary analysis

The primary analysis will consist of a repeated-measures linear mixed model including leg pain scores at each post-randomisation follow-up survey, thus allowing every participant with at least one measurement to be included in the primary analysis. The model will include the randomised intervention, the baseline leg pain score and the follow-up period as a categorical variable. An interaction term between visit and intervention will be included to allow the intervention effect to be estimated separately at each time point. The primary endpoint will be the main effect of the intervention at 12 weeks post-randomisation and will be estimated from the model as the mean difference and its 95% CI. Multiple imputation will be performed to handle missing data if required.

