### Assignment of interventions: allocation/randomisation

An independent statistician not involved in any other aspect of the study will generate the randomisation sequence a priori using a computerised random number generator. Random allocation to either duloxetine or placebo will occur in a 1:1 ratio using randomly permuted blocks of various sizes. Study medication packs will be manufactured and labelled according to the randomisation sequence by the investigational medicinal product management company, Syntro Health. Medication packs will be allocated to the various recruitment settings (ie, general practice or specialist clinics, hospital or community) in complete block sizes. The study medication packs will be dispensed direct to the participant via a central pharmacy service provided by Syntro Health, except for those participants recruited from the hospital setting whose study medication will be dispensed via the hospital’s clinical trials pharmacy. The study medication packs will be dispensed sequentially from within the blocks allocated to the respective recruitment setting.

The participant will be enrolled into the study after the informed consent process has been completed and the participant has met all inclusion criteria, and none of the exclusion criteria and study medication has been prescribed for them. The participant will be dispensed a study medication pack with a unique study enrolment number. Randomisation will occur when the medication pack is allocated to the participant during dispensing.

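### Randomisation is in effect stratified by recruitment setting, but the primary model as listed leaves setting out; if setting is prognostic, standard errors will be slightly too wide

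*Protocol article*

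**What the plan says.** The protocol article's section on allocation and randomisation describes equal allocation to the two arms by permuted blocks whose size varies. Whole blocks are then assigned to each of three kinds of recruitment setting: general practice or specialist clinic, hospital, and community. On what happens when a participant is enrolled, it says: "The study medication packs will be dispensed sequentially from within the blocks allocated to the respective recruitment setting".

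The Primary analysis section describes a repeated-measures linear mixed model and names its terms. On the main effects it says: "The model will include the randomised intervention, the baseline leg pain score and the follow-up period as a categorical variable". The one further term named lets the treatment effect differ from visit to visit. Recruitment setting does not appear, and no other section adds it. The Secondary analysis section uses the same model for leg pain at the other time points and for the continuous secondary outcomes.

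The Statistical methods section refers to a separate analysis plan, to be published before database lock. It is not at hand.

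**The concern.** When each setting draws from its own blocks, the two arms are balanced within every setting. Differences in outcome between settings therefore largely cancel from the treatment comparison. A model without setting does not take this into account. It leaves the between-setting variation in the residual and computes the standard error as if arms could be imbalanced by setting.

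If setting carries prognostic information beyond baseline leg pain, the reported standard error then exceeds the real sampling variability of the estimate. Intervals are too wide and the test runs below its nominal level. Such a difference is plausible, since the settings run from emergency departments and inpatient wards to people who answered a social-media advertisement, but the article does not quantify it.

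At stake is a small amount of precision in the primary result and in each continuous secondary result. The validity of the trial is not at stake.

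**Working it through.** **Inputs.** From the Sample size section: "A sample size of 266 patients (133 per group) provides 90% power to detect a 1-point difference in leg pain intensity"; "The calculation assumes a SD of 2.5 based on previous duloxetine trials for back pain"; and it "uses a two-tailed alpha level of 5" per cent. The same section gives a group-sequential maximum of 282, 15% dropout and a recruitment target of 332. The share of residual week-12 variance explained by setting, after baseline pain, is called R² here. The documents give no value, so it is an assumption and is varied from 0 to 10%. SD 2.5 is taken as the residual SD of the model without setting.

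**Reproducing the plan's figures.**
- Normal approximation: n per arm = 2 × (1.960 + 1.282)² × 2.5² / 1² = 131.3, rounded up to 132 (264 in total).
- With the t distribution: 132.3, rounded up to 133 per arm, or 266. This matches the article. Power at 133 per arm is 90.4% (normal) or 90.1% (t).
- Dropout: 282 / 0.85 = 331.8, rounded up to 332. This matches too.

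The calculation uses the plain SD and takes no credit for covariate adjustment.

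**Effect of omitting setting**, at 133 per arm:
- Reported SE without setting: SE₀ = 2.5 × √(2/133) = 0.307.
- Reported SE with setting: SE₁ = SE₀ × √(1 − R²). Because of the blocking, this is also close to the true sampling SD of the estimate under either model.
- Excess width: SE₀/SE₁ = 1/√(1 − R²).
- True two-sided size without setting: 2 × [1 − Φ(1.960/√(1 − R²))].
- Power for a 1-point difference: Φ((1 − 1.960 × SE₀)/SE₁) without setting, Φ(1/SE₁ − 1.960) with it.

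| Assumed R² | SE without | SE with | Excess | True size without | Power without | Power with |
|---|---|---|---|---|---|---|
| 0% | 0.307 | 0.307 | 0% | 5.0% | 90.4% | 90.4% |
| 1% | 0.307 | 0.305 | 0.5% | 4.9% | 90.5% | 90.6% |
| 2% | 0.307 | 0.303 | 1.0% | 4.8% | 90.6% | 90.9% |
| 5% | 0.307 | 0.299 | 2.6% | 4.4% | 90.9% | 91.7% |
| 10% | 0.307 | 0.291 | 5.4% | 3.9% | 91.5% | 93.0% |

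From unrounded values, the power difference is about 0.2 points at R² 1%, 0.8 at 5% and 1.5 at 10%. The half-width of the 95% interval is 0.601 without setting, against 0.598, 0.586 and 0.570 with it at R² of 1%, 5% and 10%.

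**Check by simulation.** 10,000 runs per scenario, N = 266, one time point, three settings of assumed sizes 106, 54 and 106, blocks of assumed sizes 2, 4 and 6.
- R² 10%: the model without setting reported a mean SE of 0.307 against an actual sampling SD of about 0.290, with size 3.7% and power 91.2%. With setting, the SE was 0.291, size 4.9% and power 92.8%.
- R² 5%: size 4.6% without and 5.2% with setting; power 90.9% and 91.8%.
- R² 0%: the two models behaved alike.

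**The case against.** **It may be settled in the analysis plan.** The article lists terms that will be included and does not say that there are no others, so the plan may add setting. That is possible. But the article does not leave the covariates open: it names them, including the one baseline adjustment, and omits the factor its own allocation balances on. The point therefore stands as a choice the article has fixed.

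**The loss is conditional.** This is correct. Everyone enrolled has at least 3 months of leg pain of at least moderate intensity, all sites follow the same procedures, and baseline pain is already in the model. Setting may add little. A reader might infer that lost precision is an established consequence; the documents do not support that.

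**The cost is easy to overstate.** At the maximum of 282, an R² of 5% or 10% could be described as throwing away about 14 (282 × 0.05) or 28 (282 × 0.10) participants. Those figures describe the width of the reported interval only. Blocking has already reduced the true variance, so the unadjusted test keeps part of the gain. At 141 per arm, power is 92.4% against 93.1% at R² 5%, and 93.0% against 94.3% at R² 10%. That is equivalent to about 8 and 17 participants.

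**The interim looks.** A reader might also infer that the omission distorts the stopping decisions. The Sample size and Data monitoring sections describe the boundaries and the board's review, but neither names the model used at the interims. The documents do not establish that effect.

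**No planned property fails.** This also stands. Type I error stays at or below 5%, the estimate is unbiased, and power at 133 per arm is at least 90% at every R² considered, with setting omitted.

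**Conclusion.** The mismatch between the allocation scheme and the listed model is clear from the text. Its consequence depends on an unknown. If setting predicts week-12 leg pain beyond baseline pain, the reported standard errors and intervals are somewhat too wide and the test is slightly conservative, by the amounts tabulated above. If setting is not prognostic, there is no cost at all.

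The sizes rest on the assumed R², on SD 2.5 as the residual SD, and on a single-time-point approximation to the mixed model. The error runs in the safe direction: it cannot produce a false positive finding, and it leaves the sample size justification intact. This is a modest improvement available at almost no cost, and not a defect that threatens the trial's conclusion.

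**What to change.** Add recruitment setting as a fixed categorical covariate with the three levels used for allocation (general practice or specialist clinic, hospital, community) to the primary mixed model and to the models for continuous secondary outcomes that reuse it. If the interim analyses use the same model, include it there too. Take the level from the setting whose block the pack was drawn from, so that the covariate matches the randomisation.

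The cost is one line in the analysis plan and two degrees of freedom. The variable is already known from pack allocation. If setting proves not to be prognostic, the standard error is essentially unchanged. The term should be specified before unblinding, because adding it later would look driven by the data. Publication of the analysis plan before database lock gives the occasion.

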#### Secondary analysis

The same model will be used to obtain estimates of the main effect of duloxetine at other time points for the primary outcome and for all time points for the secondary outcomes of a continuous nature. Adverse events will be classified, and the proportion of patients with adverse events and serious adverse events overall and within each category will be compared between groups using the Chi-square test.

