## Abstract

**Introduction:**

Sciatica is a debilitating condition that often becomes chronic, and for which there are few effective treatment options. Treatments such as the anti-depressant duloxetine have shown promise, but the evidence is inconclusive. We are describing a high quality, definitive trial to investigate the efficacy, safety and cost-effectiveness of duloxetine in chronic sciatica.

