To resolve the current uncertainty, we plan to conduct the duloxetine for chronic sciatica (DREAM) trial, a randomised placebo-controlled trial to investigate the efficacy and safety of duloxetine for chronic sciatica. The DREAM trial will provide high-quality evidence on the efficacy of duloxetine for sciatica, addressing a key research priority in the field.^27^

The primary aim of DREAM is to investigate the efficacy of duloxetine, compared with placebo, on leg pain intensity in people with chronic sciatica. The secondary aims are to investigate its efficacy in improving other key patient reported outcomes (including low back pain, disability, quality of life, symptoms of depression, anxiety and sleep disturbance) and its safety and cost-effectiveness in this indication.

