### Data monitoring

An independent Data Safety Monitoring Board (DSMB) will be appointed by the Steering Committee. The primary objective of the DSMB is to review unblinded safety (adverse event and serious adverse events) data and advise the DREAM Steering Committee Chair if any change to the study is recommended. The DSMB will also review data from the pre-planned interim analyses and recommend whether the trial should be stopped early according to the pre-specified group sequential design.

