## Discussion

Each year thousands of Australians suffer with sciatica, and many of these have chronic pain. For those with chronic sciatica, there are very limited treatment options—none are simple, low cost and provide meaningful reductions in their levels of pain. We identified that duloxetine is a promising treatment for chronic sciatica, but there is an urgent need for a high-quality trial that will provide a definitive answer to this question.

This manuscript describes the design of the DREAM study which aims to address this gap in evidence. The DREAM study, a randomised, double-blind, placebo-controlled trial, will evaluate the effectiveness, safety and cost-effectiveness of duloxetine 60 mg per day in chronic sciatica when taken for 12 weeks. If found effective and safe, the results of the DREAM study would be a major advance in the field and a game changer in the management of chronic sciatica. Duloxetine will be the only simple, low-cost, intervention with robust and definitive evidence of effectiveness for chronic sciatica.

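### Harms are to be compared by a Chi-square test with no effect estimate or interval named, and in a trial sized on pain a non-significant result says little about uncommon harms

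*Protocol article*

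**What the plan says.** The between-group analysis of harms is one sentence in the protocol article, under Secondary analysis: after adverse events are classified, "the proportion of patients with adverse events and serious adverse events overall and within each category will be compared between groups using the Chi-square test". No measure of effect and no interval is attached to that comparison.

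The Primary analysis section treats leg pain differently: the 12-week effect "will be estimated from the model as the mean difference and its 95% CI".

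Safety is part of what the trial sets out to answer. The Introduction lists among the secondary aims "its safety and cost-effectiveness in this indication", the abstract describes a "definitive trial to investigate the efficacy, safety and cost-effectiveness of duloxetine in chronic sciatica", and the Discussion says: "If found effective and safe, the results of the DREAM study would be a major advance in the field".

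The Sample size section rests on leg pain, with a check on disability. It gives no adverse event rate and no power for harms.

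Two other passages bear on the point. Data monitoring says: "The primary objective of the DSMB is to review unblinded safety (adverse event and serious adverse events) data". Statistical methods says of the analysis: "It will be guided by a prespecified statistical analysis plan which will be made public prior to database lock".

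**The concern.** A Chi-square test returns a p-value. It does not show how large a difference in harm is, or how large a difference the data still allow. For a question about safety, the second quantity is the useful one: the largest excess risk that the trial cannot rule out.

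This matters most for serious adverse events and for the less common adverse event categories. Event counts there will be small, and a non-significant result is likely whether or not the drug raises the risk. If the report follows the stated method literally, it gives p-values for harms beside an estimate and interval for benefit, and the two cannot be weighed on the same footing.

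**Working it through.** **1. The plan's own figures.** Inputs from Sample size: difference 1 point, SD 2.5, two-sided alpha 5%, power 90%. Per arm, n = 2 × 2.5² × (1.960 + 1.282)² / 1² ≈ 131.4, so 132 by the normal approximation. The t-test solution is 132.3, which rounds up to the stated 133, with power 90.4%. Dropout: 282 / 0.85 = 331.8, so 332 as stated. These figures reproduce, and none of them concerns harms.

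**2. Denominators for harms.** Allocation is 1:1. The article analyses participants as randomised, so the largest harms denominator is 332 / 2 = 166 per arm. The "a maximum sample size of 282 participants" (141 per arm) is the number before the dropout allowance. The expected size with early stopping is 208 (104 per arm), also before that allowance. Applying the same 15% gives 208 / 0.85 ≈ 245, or about 122 per arm.

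**3. Chance of missing a true doubling.** The documents give no placebo rate, so a range is assumed. For events X ~ Bin(n, p) on placebo and Y ~ Bin(n, 2p) on duloxetine, the test rejects when |X − Y|/n divided by √[p̄(1 − p̄) × 2/n] exceeds 1.96, with p̄ = (X + Y)/(2n). The miss probability is one minus the total probability of all (X, Y) pairs that reject (exact enumeration, uncorrected Pearson test, two-sided 5%).

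| Assumed rates, placebo v duloxetine | 166 per arm | 141 per arm | 122 per arm | 104 per arm |
|---|---|---|---|---|
| 1% v 2% | 90% | 91% | 93% | 94% |
| 2% v 4% | 83% | 85% | 87% | 88% |
| 3% v 6% | 74% | 78% | 81% | 84% |
| 5% v 10% | 59% | 65% | 69% | 72% |
| 10% v 20% | 27% | 34% | 40% | 47% |

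A continuity correction raises the 2% v 4% figure at 166 per arm from 83% to 90%. About 2,282 participants in total would be needed for 80% power at 2% v 4%.

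**4. What an interval would show.** Take, as invented data, 6/166 serious adverse events on duloxetine and 3/166 on placebo: 3.6% v 1.8%, a difference of 1.8 percentage points. The pooled proportion is 9/332 = 0.0271, so z = 0.0181 / √(0.0271 × 0.9729 × 2/166) = 1.01 and p = 0.31. The Newcombe 95% CI for the risk difference runs from −2.1 to +6.0 percentage points. The p-value alone does not tell the reader that an excess of 6 points is still compatible with the data.

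**5. Validity of the test at small counts.** The same enumeration with equal rates in both arms gives a type I error at or below 5% for placebo rates of 1% to 5% at 104, 141 and 166 per arm (for example 4.5% at a 2% rate and 166 per arm). The test is therefore not shown to give too many false positives there. The problem is that it says little, not that it is invalid.

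**The case against.** The strongest reply is that a journal article condenses the plan, that effect measures for harms belong in the statistical analysis plan, and that this plan is promised before database lock. That carries weight: intervals may already be intended, and nothing in the article excludes them. But the article is not silent on the method. It chooses a test for harms and, in the section before, an estimate with an interval for pain. The method it names can be judged, and an analysis plan written to match it would carry the weakness forward.

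A second reply is that low power for rare harms is normal in a trial sized on efficacy, and that intervals will not change it. This is correct. The miss rates show why a p-value is a poor summary here; they are not an argument for a larger trial. If percentages per arm are published, readers can also derive an interval themselves, which lessens the harm.

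Some stronger readings are tempting and are not supported:

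- **That safety will be concluded from a non-significant test.** The article gives no such rule. The Discussion sentence is conditional and sets no criterion, so it needs no rewording on this account.
- **That the Chi-square test is the only judgement of safety.** The monitoring board reviews unblinded events and an independent medical monitor assesses serious ones. Neither is described as producing the reported between-group comparison, so the test remains the only such comparison stated.
- **That a doubling of serious events is missed 83% to 85% of the time, as a fact about this trial.** That holds only for an assumed placebo rate of 2%, at 166 and 141 per arm.
- **That testing the 21 checklist items gives about a 66% chance of a false signal** (1 − 0.95²¹). This assumes 21 independent tests, and the article does not plan to test each item as a category.

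**Conclusion.** The point holds as a cheap improvement to a stated method. The one between-group comparison of harms that the article names is a bare significance test, in a trial that counts safety among its aims. Over assumed placebo rates of 1% to 10%, that test would miss a true doubling about 90% down to 27% of the time at the maximum of 166 per arm, and more often after early stopping.

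The size rests on three assumptions: the placebo rates, which the documents do not give; a two-sided 5% level for the harms test, which the article states only for the sample size; and full counting of everyone randomised. The conclusion about reporting depends on none of them, because an estimate with an interval tells the reader more than a p-value at any event rate.

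**What to change.** In Secondary analysis, and in the statistical analysis plan, replace the Chi-square sentence with wording such as: For adverse events and serious adverse events, overall and by category, the number and percentage of participants in each arm will be reported with the risk difference, the risk ratio, or both, and 95% CIs, using score or exact methods where counts are small. Category-level comparisons are descriptive. A non-significant difference will not be read as evidence of safety.

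The cost is two or three sentences and slightly longer harms tables, from data already being collected. The trade-off is a more modest claim about rare harms. Power for such harms stays as it is.
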